### Why do ACP in healthcare settings?

The lack of ACP discussions increases the risk that veterans will receive care different from what they prefer and may experience unnecessary interventions leading to increased suffering and higher health care costs [4, 5]. While VHA Handbook 1004.02 mandates personalized ACP discussions including information on AD for all patients in all VHA settings to comply with the Patient Self-Determination Act of 1990 and the Joint Commission, documentation of these discussions in VHA is challenging. This may be due to patient and provider barriers, such as a lack of veteran awareness and lack of perceived clinical priority by providers, respectively [6]. Also, in our clinical experience [7–9], ADs of VHA patients are difficult to quantify using electronic health records or administrative data retrieval systems since they are scanned or hard copy documents. Given these barriers, a new data architecture system launched in FY 20 will provide a national view of ADs across the VHA. Future studies will compare the VA to the community AD completion rate of 26% [10], yet current estimates using this community rate note that 6.7 of the 9.05 million enrolled veterans do not have an AD and may be hospitalized without their medical preferences being known.

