### Sample

The population for this evaluation potentially includes all veterans who seek care in FY 2019 in VHA (*N* = 9.05 million). The total number of VHA facilities is approximately 170 sites. All veterans who seek VHA services are eligible to receive information on ACP and can complete an AD. Some veterans may choose to engage in an ACP discussion individually while others may elect to attend a group visit. While all veterans are eligible, not all veterans will engage in ACP discussions or ever complete an AD. Using VA administrative data, we will examine all documented ACP discussions, AD completions, and ACP-GV encounters to estimate the sample. In FY 2019, there were 23 funded sites and 12 unfunded sites (i.e., no funding for dedicated staff positions), for a grand total of *N* = 35 sites.

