## Aim 1: Evaluate the impact of the ACP-GV National Program on the proportion of ACP discussions in VHA by comparing ACP-GV sites to propensity score-matched control sites not implementing ACP-GV

### Design

The 35 ACP-GV sites will be considered “intervention” sites. We will identify a set of matched “control” sites (*N* = 35) defined as VHA facilities not implementing ACP-GV based on an analysis of the ACP-GV workload specific code in VA Corporate Data Warehouse data and not participating in the National Program implementation activities but documenting ACP discussions as noted in the VA Corporate Data Warehouse and using AD note titles. Our hypothesis is that ACP-GV sites (i.e., intervention sites) will have a higher proportion and significantly greater quarterly and annual rates of ACP discussions compared to the PS-matched control sites. Given that the sites were not randomized to either the intervention or control, we will use PS matching to create a “pseudo” randomized evaluation design. The PS is a model-based conditional probability of a site’s membership in the intervention, given its observed site characteristics [21]. We will use a logit model to estimate the PS for each site. The dependent variable of the logistic regression model is being/not being in the ACP-GV intervention group. The independent variables are site characteristics including: rurality, geographic location, Veterans Integrated Service Network (VISN), staffing, facility size, and aggregate veteran demographics such as age, gender, and race/ethnicity. We will use a greedy matching algorithm based on 5-to-1 digit matching [22]. An initial ACP-GV site will be randomly selected from the existing sites to start the process. A non-ACP-GV site (i.e., control) with the closest PS that lies within a fixed distance will be selected for matching. If multiple control sites have PS that are equally close, then one of the control sites will be selected at random. The process will continue until all ACP-GV sites that can be matched have been matched. To evaluate the success of the PS matching, we will compare the balance in the distributions of all the observed site covariates between the two groups using standardized difference plots. An absolute standardized difference of less than 10% suggests a negligible imbalance between the two groups for a given site covariate [23]. A PS matching limitation is if no control sites have PS that lie within the predefined distance (i.e., caliper) of an intervention site, then that ACP-GV site is not included in the PS-matched sample. Given sample size limits, if the PS matching produces a limited number of pair matches, we will consider other strategies, (e.g., PS through stratification, covariate adjustment with PS, or inverse PS weighting).

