
### Data analysis for aim 1

We will aggregate patient-level outcomes of the ACP discussions and site characteristics (e.g., geographic location, facility size, rurality, etc.) across VHA sites quarterly and annually for descriptive purposes, and then compare the proportion of ACP discussions with the PS-matched control sites. We will specifically examine sites with a high annual rate of ACP discussion and low ACP-GV rates and vice versa to identify patterns and trends. We will present numerical variables as means (SD) or medians (interquartile-range) and categorical variables as counts and percentages (with 95% confidence interval). We will use a significance level of 0.05. To compare annual rates of ACP discussions, the primary outcome for this aim, we will use a two-sided *z*-test with pooled variance to test the difference in proportions across the two groups (i.e., ACP-GV vs. non-ACP-GV). As a secondary analysis, multivariable Poisson regression will examine the differences in annual rates of ACP discussions, while accounting for potential imbalance in site characteristics. Given the sample size, we will build a parsimonious model based on forward model selection.

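### The Aim 1 primary test is a pooled-variance z-test on proportions with no between-facility variance, although facilities are the exposed and matched units, so the 0.05 level does not hold

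*Protocol article*

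**What the plan says.** The Design section of Aim 1 makes the facility the unit of exposure and of matching. The 35 ACP-GV sites form the intervention group, the target is 35 control sites, the propensity score models a site's membership from site characteristics, and pairs are formed greedily within a caliper: "The process will continue until all ACP-GV sites that can be matched have been matched". If few pairs result, stratification, covariate adjustment or inverse weighting on the propensity score is allowed instead.

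Data analysis for aim 1 starts from patients: "We will aggregate patient-level outcomes of the ACP discussions and site characteristics". It describes the quarterly and annual site aggregation as descriptive. It then fixes the primary test: "To compare annual rates of ACP discussions, the primary outcome for this aim", a two-sided z-test is used "with pooled variance to test the difference in proportions across the two groups". The error rate is also fixed: "We will use a significance level of 0.05". A multivariable Poisson regression with site characteristics is secondary. Neither section mentions a facility effect, a robust variance, a design effect or a paired comparison.

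**The concern.** A pooled-variance test of two proportions estimates the variance of the difference as p(1−p)(1/n₁ + 1/n₂). That is correct when each unit counted in n is an independent yes/no observation. Here veterans in the same facility share staff, local practice and documentation habits, and the whole facility is either in the program or not. The article itself expects facilities to differ: the Aim 1 analysis looks for sites whose discussion rates and group-visit rates diverge, and Aim 4 selects sites from the upper quarter of the national distribution.

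At stake is the only controlled comparison of program impact in the evaluation. If between-facility variation is left out, ordinary differences between two sets of 35 facilities can be reported as a significant effect of the program, with a confidence interval that is far too narrow. This is not a detail left to an analysis plan. The article names the primary test, and a later plan could correct it only by departing from the article.

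**Working it through.** The article states no sample size, power, ICC or baseline rate, so there is no planned figure to reproduce. The one fixed quantity is the two-sided 0.05 level, and the check is whether the named test keeps it.

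**Inputs from the article**
- Sites per group: 35 (Aim 1, Design).
- Population: 9.05 million veterans in about 170 facilities (Sample: "The population for this evaluation potentially includes all veterans who seek care in FY 2019 in VHA"). Mean site size m = 9,050,000/170 ≈ 53,235, so 35 × 53,235 ≈ 1.86 million veterans per group.

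**Assumptions**
- ICC 0.001 to 0.01. At an assumed 10% discussion rate, the between-site SD is √(ICC × 0.10 × 0.90): 0.95 percentage points at ICC 0.001 and 3.0 points at 0.01.
- Site sizes of 10,000 and 1,000 are also tried, because the national mean need not describe the sites in the comparison.

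**Reading 1: n counts veterans**

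Design effect DE = 1 + (m − 1) × ICC. Actual type I error = 2 × [1 − Φ(1.96/√DE)].

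| Veterans per site | ICC 0.001 | ICC 0.01 |
|---|---|---|
| 53,235 | DE 54.2, error 79% | DE 533.3, error 93% |
| 10,000 | DE 11.0, error 55% | DE 101.0, error 85% |
| 1,000 | DE 2.0, error 17% | DE 11.0, error 55% |

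At 53,235 per site the standard error is too small by √54.2 ≈ 7.4 to √533.3 ≈ 23. At a 10% rate the z-test calls a difference of 0.06 percentage points significant (1.96 × 0.031). With between-facility variance included, the smallest significant difference is about 0.46 points (ICC 0.001) or 1.4 points (ICC 0.01).

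**Simulation under no true difference** (beta-binomial, 35 pairs, mean site size 53,235 with CV 0.5, 10% rate, 4,000 runs per row; percentage of runs rejecting):

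| ICC | Pair correlation | Pooled z, veterans | Unpaired t on site proportions | Paired t on site proportions |
|---|---|---|---|---|
| 0.001 | 0 | 81 | 4.4 | 4.4 |
| 0.001 | 0.5 | 75 | 0.6 | 5.0 |
| 0.01 | 0 | 94 | 5.5 | 5.2 |
| 0.01 | 0.5 | 93 | 0.7 | 4.5 |

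The simulation agrees with the formula. Successful matching reduces the inflation only a little.

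**Reading 2: n = 35 sites per group in the binomial variance**

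The test then uses p(1−p) × 2/35. At p = 0.10 its standard error is √(0.18/35) = 0.0717, so a difference of 1.96 × 0.0717 ≈ 14 percentage points is needed. The true between-site SD is only 0.95 to 3.0 points. In the same simulation this version rejected in none of the 4,000 runs in any row.

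**The case against.** The strongest reply is that the article never states the unit of analysis. It speaks of limited sample size in both Aim 1 sections, which fits about 70 sites better than millions of veterans. A third reading then exists: a z-test that uses the pooled variance of the 35 + 35 observed site proportions. That variance does include facility differences. With uncorrelated pairs its type I error is close to nominal: 5.4% in theory (normal cut-off with 68 degrees of freedom) and 5.2% to 5.3% in simulation. The unit is indeed inferred, and this part of the reply stands. But this is not what a pooled-variance test of a difference in proportions ordinarily means, and the site aggregation is labelled descriptive. A primary analysis should not depend on a reader choosing the unusual meaning.

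It also stands that the size of the inflation depends on an ICC and a site size that the article does not give. Funded sites are rural, so the national mean may overstate their size.

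Two further inferences are tempting and should not be drawn:
- That ignoring the pairs causes false positives. It does not. When pairs are correlated, the unpaired site-level test is conservative (0.6% to 0.7% above). Pairing is a secondary matter of efficiency.
- That the Aim 1 denominator is contradictory, because the 9.05 million are described once as seeking care and once as enrolled ("6.7 of the 9.05 million enrolled veterans do not have an AD"). The latter is background arithmetic on advance directives, and neither passage defines the Aim 1 denominator.

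**Conclusion.** The concern holds. The named primary test does not fit a design in which facilities are exposed and matched. On the ordinary reading it omits between-facility variance, and the 0.05 level is not kept: 79% to 93% at the article's mean site size, 55% to 85% at 10,000 per site and 17% to 55% at 1,000 per site, for an assumed ICC of 0.001 to 0.01. With n = 35 in the binomial formula it fails in the opposite direction and almost never rejects.

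A reader might infer that the test rejects whatever the truth is, or that a significant result would be worthless. The article does not support either. The inflation is conditional on the veteran-level reading and on unstated quantities, and an understated variance does not by itself bias the estimated difference. What fails is the significance level and the interval width.

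**What to change.** - Replace the pooled z-test with one prespecified primary analysis whose variance comes from differences between facilities, and name the unit of analysis. A paired t-test or paired regression on site-level proportions suits the planned pair matching.
- State the corresponding site-level comparison for the fallback propensity-score methods, where no pairs may exist.
- A patient-level model with facility clustering and a small-sample correction is an alternative, not an equivalent: it weights sites differently and can target a different estimand. Choose one in advance.
- Give the secondary Poisson model a facility-level or overdispersion-robust variance.

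The cost is analysis wording. The data are the same. The interval will be wider, but its stated coverage will be credible.

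### Aim 1's secondary Poisson regression with forward selection makes no allowance for between-site variation, so with model-based standard errors its group test and selection steps are anti-conservative

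*Protocol article*

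**What the plan says.** Under Data analysis for aim 1, the primary comparison of annual discussion rates is a two-sided pooled z-test. As the secondary analysis, "multivariable Poisson regression will examine the differences in annual rates of ACP discussions, while accounting for potential imbalance in site characteristics". The model-building rule follows: "Given the sample size, we will build a parsimonious model based on forward model selection". The entry criterion is not given. On error rate: "We will use a significance level of 0.05".

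The Aim 1 Design section sets the size. "The 35 ACP-GV sites will be considered" intervention sites, and up to 35 matched controls are sought, so there are at most 70 sites, fewer if some program sites find no match.

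The article names no dispersion parameter, robust variance, site effect or negative binomial alternative for this model. Elsewhere it treats differences between sites as real. The aim 1 analysis contrasts high-rate with low-rate sites, the Aim 4 sampling plan picks sites in the top national quartile for discussions, and the Discussion sets out to study natural variation in implementation.

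**The concern.** A Poisson model takes the variance of a site's count to equal its mean once covariates and population are accounted for. Facilities differ in documentation habits, leadership, staffing and case mix, and a small model on 70 sites cannot absorb all of that. The excess variance grows with the count, so the problem is worst where counts are large.

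Two things follow if the standard errors come from the Poisson model itself. The group comparison is declared significant too often when there is no program effect. Forward selection, if entry rests on those same standard errors, also admits covariates with no relation to the outcome.

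A further mismatch does not depend on the variance. The model is there to adjust for imbalance remaining after matching, yet forward selection picks covariates by their association with the outcome, not by their imbalance between groups.

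At stake is whether the adjusted analysis can serve as a check on the primary result. The primary z-test has no site term either. If it pools patients, a falsely significant adjusted result would appear to confirm a test with the same weakness.

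**Working it through.** The article states no power, error rate, discussion rate or between-site variance for this analysis, so there is no figure to reproduce.

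**Inputs from the article**
- 35 program sites and up to 35 controls (Aim 1, Design).
- Significance level 0.05 (Data analysis for aim 1). The group test is taken as two-sided; the article does not say.
- 9.05 million veterans and about 170 facilities (Sample): 9,050,000 / 170 = about 53,235 per facility.

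**Assumptions, not in the article**
- Mean annual discussions per site, μ: 100 to 5,000. On 53,235 veterans these are rates of 100 / 53,235 = 0.19% to 5,000 / 53,235 = 9.4%. A count of 1,000 needs 1.9%.
- Residual between-site CV of the true rate, c: 0.05 to 0.3.
- Site-level counts. The article describes aggregation by site but does not state the unit of this model. With site-level covariates only, a patient-level Poisson fit gives the same estimates and model-based standard errors.

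**Step 1: type I error of the group test.** The variance of a site count is μ(1 + μc²) = φμ. A test that takes φ = 1 has standard errors too small by √φ, and its type I error is 2[1 − Φ(1.96/√φ)].
- μ = 100, c = 0.05: φ = 1.25, 1.96/1.118 = 1.753, type I error 0.08.
- μ = 1,000, c = 0.1: φ = 11, 1.96/3.317 = 0.591, type I error 0.555.
- μ = 5,000, c = 0.3: φ = 451, 1.96/21.24 = 0.092, type I error 0.926.

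| Discussions per site | c = 0.05 | c = 0.1 | c = 0.3 |
|---|---|---|---|
| 100 | 0.080 | 0.166 | 0.535 |
| 500 | 0.191 | 0.424 | 0.773 |
| 1,000 | 0.295 | 0.555 | 0.837 |
| 5,000 | 0.594 | 0.784 | 0.926 |

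With c = 0 it is 0.05 at every count.

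**Step 2: forward selection, by simulation.** 35 against 35 sites, no group effect, gamma-distributed site rates, log population as offset, eight pure-noise covariates, entry at |z| > 1.96 (assumed), 100 data sets per setting. Pearson scaling, where used, applies to selection and to the final test.

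| μ, c | Poisson: group rejected | Poisson: noise kept of 8 | Scaled: group rejected | Scaled: noise kept of 8 |
|---|---|---|---|---|
| 1,000, 0 | 0.05 | 0.46 | 0.06 | 0.51 |
| 1,000, 0.1 | 0.64 | 4.63 | 0.10 | 0.49 |
| 1,000, 0.3 | 0.82 | 6.77 | 0.11 | 0.64 |
| 5,000, 0.1 | 0.81 | 6.59 | 0.10 | 0.74 |
| 5,000, 0.3 | 0.91 | 7.46 | 0.08 | 0.76 |

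The Monte Carlo standard error of a rejection rate is at most √(0.25/100) = 0.05, and about √(0.1 × 0.9/100) = 0.03 near 0.10. In the overdispersed settings plain Poisson kept 4.63/8 = 58% to 7.46/8 = 93% of the noise covariates.

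**Step 3: how much is due to the variance and how much to the search.** With 600 null data sets per setting (400, 1,000 and 2,662 per site; c = 0.1 and 0.3), scaling the variance of the group term gave rejection rates of 0.06 to 0.08. In 400 null data sets at 2,662 per site (an assumed 5% of 53,235), the mean group log rate ratio after plain Poisson selection was 0.003 (c = 0.1) and 0.005 (c = 0.3). Its standard deviation was 0.026 when most noise covariates were kept against 0.025 when few were (c = 0.1), and 0.077 against 0.071 (c = 0.3). Most of the error is therefore in the variance; the estimate barely moves.

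**The case against.** The strongest reply is that the article names only a model family. It does not say model-based standard errors, and it does not rule out a scaled or robust variance. Such detail commonly sits in an analysis plan, and none is shown. This stands as a condition on the point: a robust or scaled variance would largely repair the group p-value. It would not remove the forward-selection rule, which the article states outright.

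The size also rests on two unknowns. A reader might infer from 53,235 veterans per facility that counts run into the thousands. The article does not support that as a fact: it gives no discussion rate, the 9.05 million is elsewhere described as enrolled veterans, and funded sites are rural and may be smaller than average. At 100 discussions per site and a CV of 0.05 the error is 0.08, a modest inflation.

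A reader might also infer that forward selection has been shown to corrupt the group estimate. It has not. The simulation contains no confounders, and the estimate stayed near zero with almost unchanged spread. The case against forward selection rests on its mismatch with the stated purpose and on the failure of parsimony under Poisson errors, not on demonstrated bias.

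Nor is this model the plan's only response to imbalance. The Design section also sets a standardized-difference check and lists stratification, covariate adjustment and weighting by propensity score, although these are triggered by too few matched pairs.

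Finally, the analysis is secondary. If the primary z-test pools patients, the same omission matters more there.

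**Conclusion.** The point holds, conditionally on model-based standard errors. The article fixes a Poisson regression with forward selection on at most 70 sites, expects site rates to differ, and names nothing to carry that variation. Over the assumed range of 100 to 5,000 discussions per site and a residual CV of 0.05 to 0.3, type I error is about 0.08 to 0.93. At 1,000 or more per site with a CV of 0.1 or more it is at least 0.55, and forward selection retained more than half of the pure-noise covariates in every such setting simulated.

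A reader might go further and call the adjusted result meaningless. That is too strong. Overdispersion does not invalidate the rate ratio, and the damage to the p-values depends on a count and a CV that the article does not give. The need is for a stated variance method, supported by a fixed covariate set. As a secondary analysis, this should be changed but does not by itself undermine the evaluation.

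**What to change.** Replace the secondary model with quasi-Poisson or negative binomial regression on site-level annual counts, with the log of veterans seen as offset and site-level standard errors corrected for the small number of sites. Report the rate ratio with its 95% confidence interval.

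Replace forward selection with a short list of site covariates fixed before outcome data are examined, drawn from those already in the propensity model, such as rurality, facility size and mean age. Adding the pre-program discussion rate or keeping the matched pairs in the model is optional; neither was tested here.

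The variance model is the core change and the fixed list supports it. No new sites are needed, and the only data added beyond the current plan would be the optional pre-program rate. The cost is a reworded analysis paragraph, a wider interval and less flexibility in choosing covariates. If an analysis plan already names an overdispersion-robust variance, stating it in the protocol settles the first part.

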## Aim 2: Among ACP-GV sites, document and compare ORH-funded and DEI-unfunded sites on the effectiveness of implementation strategies (individual and combinations) used by sites in the ACP-GV National Program on ACP discussion and AD completion rates across the VHA

### Data analysis for aim 2

We will use a comparative case study approach to compare funded sites to unfunded sites on the two outcomes of ACP discussion and AD completion rates for aim 2. Due to the small number of sites, we are hindered in our ability to control for confounders. Yet, we anticipate that additional funding for staff positions will largely impact outcomes. Therefore, we will track the other four implementation strategies (see Table 1) to serve as mediators of impact. If funding expresses greater participation in the other strategies, then there may be a mechanism of action within accessing new funding alone, or because it is in combination with the other strategies.

In our preliminary data, there is some evidence of variation in participation in the implementation strategy of ongoing training by funded sites and increased uptake of ACP-GV vs. unfunded sites. We will use the Implementation Team Site Tracking Report and qualitative interviews from aim 3 and aim 4 to determine if we can make quantitative inferences as to what funding imbues and what impact it has on the other implementation strategies. To provide feedback to our partners for quality improvement and to not lose important trends that may exist in the data that may help understand larger trajectories of change, we will generate quarterly reports tabulating the number and type of implementation strategies used at each site per quarter and the extent to which each of the sites achieved the implementation outcomes. The annual summative evaluation report will describe the implementation strategies that were used by multiple facilities which were most successful and least successful in achieving positive outcomes. These quarterly briefs, annual reports, and our aim 4 analyses will be synthesized to support sustainability and spread of the initiative.

